## Abstract

**Background:**

To respond to the rapid surge in the incidence of suicide in Japan, which appears to be an ongoing trend, the Japanese Multimodal Intervention Trials for Suicide Prevention (J-MISP) have launched a multimodal community-based suicide prevention program, NOCOMIT-J. The primary aim of this study is to examine whether NOCOMIT-J is effective in reducing suicidal behavior in the community.

Methods/DesignThis study is a community intervention trial involving seven intervention regions with accompanying control regions, all with populations of statistically sufficient size. The program focuses on building social support networks in the public health system for suicide prevention and mental health promotion, intending to reinforce human relationships in the community. The intervention program components includes a primary prevention measures of awareness campaign for the public and key personnel, secondary prevention measures for screening of, and assisting, high-risk individuals, after-care for individuals bereaved by suicide, and other measures. The intervention started in July 2006, and will continue for 3.5 years. Participants are Japanese and foreign residents living in the intervention and control regions (a total of population of 2,120,000 individuals).

**Discussion:**

The present study is designed to evaluate the effectiveness of the community-based suicide prevention program in the seven participating areas.

**Trial registration:**

UMIN Clinical Trials Registry (UMIN-CTR) UMIN000000460.

## Background

### Recent rapid increase of suicide in Japan

#### (1) Changes in suicide incidence

According to vital statistics collected by the Japan Ministry of Health, Labour, and Welfare in 1997, there were 23,494 suicides (15,901 men and 7,593 women), with the number rising to 31,755 (22,349 men and 9,406 women) in 1998, which represented a 35% increase. This was the highest rate of increase recorded since the Ministry began tracking mortality statistics. The number of suicides remained high in subsequent years, reaching 29,949 in 2002 and 32,109 in 2003.

In 2002, the World Health Organization (WHO) reported that the suicide rate in Japan (25.3 per 100,000) was higher than in any other developed nation (for comparison: France: 17.5, Germany: 13.5, Canada: 11.7, United States of America: 10.4, United Kingdom: 7.5, Italy: 7.1).

In terms of the number of suicides, three peaks have emerged since World War II. However, the most recent rise that started in 1998 has shown no signs of abating, and represents the worst in Japan's history. Therefore, it is clear that suicide prevention measures are urgently needed in Japan.

#### (2) Regional tendencies

It has been pointed out that the suicide rate has traditionally been high in the three prefectures of the northern Tohoku area (Akita, Iwate, and Aomori), Niigata, Shimane, and the Kyushu area (Miyazaki, Kagoshima, and Okinawa) [1].

The increase in the number of suicides that began in 1998, however, was not necessarily attributable to suicides in these rural areas. Fujita (2003) [2] conducted a comparative study of suicide rates by prefecture by comparing a time period with a low number of suicides (1989–1995) to time periods before and after, during which the number of suicides was on the rise (1983–1987 and 1998–2000, respectively). The findings indicated that the recent increase in the number of suicides has been significantly more prominent in urban areas such as Tokyo, Osaka, and their surrounding areas, than in rural areas. During the two periods 1989–1995 and 1998–2000, the mean number of suicides among people 15 years of age or older rose from 894 to 1,658 in Osaka, from 713 to 1,309 in Kanagawa, and from 1,129 to 1,938 in Tokyo.

With regard to recent trends in suicide rate by age, the middle-aged population was found to have higher suicide rates. In 2004, 42.1% of those who committed suicide were 45 to 64 years old. This tendency was particularly evident among men, in whom the suicide rate peaked at 55 to 59 years of age, whereas a similar trend was not found in women, in whom the suicide rate generally increased with age.

#### (3) Causes and motives for suicide

According to the statistics of the National Police Agency, health and financial/lifestyle problems were the top two reasons for suicide. Although this tendency remained the same during the increase in suicides that began in 1998, the number of suicides due to financial/lifestyle problems has increased more rapidly compared to suicides committed due to health problems. Among those who committed suicide with or without suicide notes in 1997, 13,659 individuals (56.0%) did so due to health problems and 3,556 individuals (14.6%) due to financial/lifestyle problems. These numbers rose to 16,769 (51.0%, a 22.8% increase over the previous year) and 6,058 (18.4%, a 70.4% increase over the previous year), respectively, in 1998. In terms of those with health problems, the number of suicides subsequently decreased in 2004 to 14,786 (45.7%), whereas the number of suicides due to financial/lifestyle problems increased to 7,947 (24.6%). This indicates that the percentage of suicides due to financial/lifestyle problems has been increasing.

### Recent suicide prevention programs in Japan

Many suicide prevention measures have been implemented internationally [3-5]. In Japan, evidence has also emerged recently to support the effectiveness of community-based programs for suicide prevention. Seven community-based intervention trials implemented for five years or more have been conducted between 1985 and 2005 in Japan. All the trials used a quasi-experimental design and included suicide rate as the primary outcome. These suicide prevention programs included the development of social support networks in the community and/or depression screening for residents with follow-up by physicians. All the intervention programs were also administered by local governments. Six of the seven trials targeted individuals aged 65 years and older.

The first trial was conducted in Matsunoyama, Niigata prefecture. During the 10-year implementation period, the suicide rate of over 150 per 100,000 decreased by 75% for both men and women aged 65 years and older [6]. In the trials conducted in Joboji (Iwate pref.), Nagawa (Aomori pref.), Matsudai and Yasuzuka (Niigata pref.), and Yuri (Akita pref.), the suicide prevention program significantly reduced the suicide risk for individuals aged 65 years and older [7-10].

Recently, a relatively large, multimodal intervention trial targeting all age groups was conducted in four municipalities of Akita. During the four-year implementation period, the suicide rate of 68 per 100,000 for all residents was reduced by 27% [11].

The results of these seven trials suggest that community-based intervention would be effective for preventing suicide and that the increase of suicide deaths in Japan may be related to more pervasive social isolation than in the past, and to an absence of personal psycho-social development compared with financial success.

However, the sample sizes in these trials were relatively small and the monitoring of the implementation process was insufficient. Furthermore, since the trials were conducted in rural areas with high suicide rates, it is still unclear whether similar community-based programs would be effective in urban areas where the suicide rates have increased rapidly. Therefore large, community-based intervention trials with adequate controls should be conducted to develop an effective, evidence-based suicide prevention program to reduce the future suicide rate in Japan.

### Objectives of this study

(1) The primary goal is to examine the effectiveness of a community-based multimodal intervention program for suicide prevention in regions where the suicide rate was relatively high compared to control regions. These target areas were designated "Group 1".

(2) The secondary goal was to explore the effectiveness of a community-based multimodal intervention program for suicide prevention in highly populated regions. These target areas were designated "Group 2".

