#### Eligibility Criteria

Target areas will be selected and divided into two groups: "Group 1" and "Group 2" as mentioned above. The areas meeting the following criteria will be eligible for the study:

a) Areas with strong support from local government and other organizations to conduct this multimodal suicide prevention program.

b) Areas capable of selecting intervention and control regions.

c) Areas capable of following the data collection procedure.

d) Areas with comparable baseline data on suicide attempts in intervention and control regions.

e) Areas with comparable baseline demographic data in intervention and control regions.

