#### Participating regions and sample size estimation

(1) Group 1: Regions in Aomori, Akita, Iwate, and the Minamikyushu area, with a total population of 670,000 individuals.

(2) Group 2: Regions in Sendai, Chiba, and the Kitakyushu area, with a total population of 1,450,000 individuals.

After a preliminary survey to record the rate of suicidal behavior and other information in the target regions in these areas, intervention and control regions will be selected based on the similarity in community characteristics and the incidence of suicidal behavior (Figure 1).

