#### Rationale for estimation of sample sizes

Sample sizes to be used in the study were calculated based on the assumptions of the outcome and suicide rates from 2002 to 2004 in Groups 1 and 2 presented in Table 1.

**Table 1 T1:** Assumptions of the outcome and suicide rates in Group 1 and Group 2

	Group 1	Group 2
Suicide rate in control regions (per 100,000 individuals)	30	20
Proportion of expected numbers of ambulance transports due to "self-harm" (severe and mild cases) relative to completed suicides	50%	50%
Expected suicide rate reduction over observed 3 years by intervention	20%	15%
Significance level (two-sided)	5%	5%

*Notes*. These assumptions of the outcome and suicide rates (2002–2004) are used to calculate the sample sizes in this study.

Group1: regions with a relatively high suicide rate compared to control regions, examined to gauge the effectiveness of the community-based multimodal intervention program for suicide prevention.

Group 2: highly-populated regions, examined in order to explore the effectiveness of the community-based multimodal intervention program for suicide prevention.

Although the estimated sample sizes are not adjusted for 5-year age group, sex, and regional characteristics, if all assumptions are met, the statistical power will be over 80% for each group, regarding person-year incidences in the intervention and control regions.

Using the O'Brien-Fleming method [12] in the interim analysis, the significance level in the final analysis is estimated to be 4.9% for a two-sided test. In addition, the statistical power will be over 80% in each group.

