##### (1) Statistics on suicide

The number of suicides in the 3 years prior to the study (2003–2005) in the study regions was recorded by sex and 5-year age group the Japan Ministry of Health, Labour, and Welfare.

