##### (2) Information from the emergency report

Information on "self-harmed" individuals transported by ambulance in the 3 years prior to the study was collected from the emergency reports of ambulance service.

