### Statistical analysis

#### Primary analysis

In the primary analysis, the incidence of suicidal behavior will be calculated based on the number of suicidal behavior per person-year for the annual population. Data obtained will include the incidence of suicidal behavior and its 95% confidence intervals adjusted by sex, 5-year age group, and regional characteristics. This data will be compared between the intervention and control regions in "Group 1".

The significance level will be set at 0.05 for the two-sided test, and will be adjusted in the final analysis based on the methods of O'Brien and Fleming [12] for interim analysis.

Additionally, regression analysis will also be performed to examine the interactions among sex, 5-year age group, and regional characteristics. A statistician in the study group will determine the analysis plan, whereas a different independent statistician will perform the interim analysis. The independent statistician will not contribute to the revision of the statistical analysis plan after interim analysis.

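### Regions are selected rather than randomised, but the stated primary adjustment set leaves out the baseline outcome rate that the trial already collects

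*Protocol article*

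**What the plan says.** **Allocation.** Under Participating regions and sample size estimation, after a preliminary survey, "intervention and control regions will be selected based on the similarity in community characteristics and the incidence of suicidal behavior". The Eligibility Criteria also require "Areas with comparable baseline data on suicide attempts in intervention and control regions", and comparable demographic data.

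**Primary analysis.** Incidence per person-year is adjusted for sex, 5-year age group and regional characteristics. Then: "This data will be compared between the intervention and control regions in" Group 1. Baseline Information, item 4, lists the regional characteristics: geography, marital status, family structure, unemployment, labour force and population turnover. No suicide or self-harm rate is among them.

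**Baseline outcome data.** Item 1 of the same section states: "The number of suicides in the 3 years prior to the study (2003–2005) in the study regions was recorded by sex and 5-year age group". Item 2 covers self-harmed individuals "transported by ambulance in the 3 years prior to the study was collected from the emergency reports". Neither the primary, interim nor secondary analysis text mentions these data.

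**Definition of Group 1.** The objectives place the primary question "in regions where the suicide rate was relatively high compared to control regions", and the Table 1 notes describe Group 1 as "regions with a relatively high suicide rate compared to control regions".

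**The concern.** In a non-randomised comparison of a small number of regions, any rate difference that existed before the programme, and that the adjustment variables do not explain, goes straight into the primary rate ratio. The region's own earlier rate of the same outcome is the most direct available control for such a difference. Here it is collected for three years, yet it is absent from the named adjustment set.

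The error can run either way. If intervention regions start higher, a real benefit is diluted or hidden. If they start lower, a benefit can appear where there is none. The sample size rationale does not allow for this, because it applies the expected reduction to the control rate and so takes the underlying rates as equal.

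**Working it through.** **Inputs from the article (Group 1).** Total population 670,000; control suicide rate 30 per 100,000; ambulance-transported self-harm at 50% of suicides, taken at face value; 20% reduction over 3 years; final two-sided alpha 4.9% (critical value 1.969).

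**Assumptions of this check.** A 1:1 split (335,000 per arm), Poisson variation only, and a range of baseline differences. The article gives neither the split nor any baseline difference.

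**Step 1: reproduce the stated power.**
- Composite rate: 30 × 1.5 = 45 per 100,000.
- Control events: 335,000 × 3 × 0.00045 = 452. Intervention events: 452 × 0.8 = 362.
- SE of the log rate ratio: √(1/452 + 1/362) = 0.0705.
- Power: Φ(0.2231/0.0705 − 1.969) = 88%.

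This agrees with the article's claim of more than 80%. Group 2 gives 80% in the same way (652 against 555 events).

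**Step 2: let intervention regions start a fraction d higher, with a true 20% reduction.** The follow-up rate ratio becomes 0.8 × (1 + d).

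| Residual excess d | Follow-up rate ratio | Events, control / intervention | SE | Power |
|---|---|---|---|---|
| 0% | 0.80 | 452 / 362 | 0.0705 | 88% |
| 5% | 0.84 | 452 / 380 | 0.0696 | 70% |
| 10% | 0.88 | 452 / 398 | 0.0687 | 46% |

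With 40% or 33% of the population in intervention regions, power at no excess is 86% or 83%, and at a 10% excess 44% or 41%. The pattern does not depend on the assumed split.

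**Step 3: no true effect.** The nominal error is 2.45% in each direction.
- 10% excess: 452 against 497 events, SE 0.0650. Probability of significant harm: Φ(0.0953/0.0650 − 1.969) = 31%.
- 10% deficit: 452 against 407 events, SE 0.0683. Probability of significant benefit: Φ(0.1054/0.0683 − 1.969) = 33%.
- A 5% difference either way gives about 11%.

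**Step 4: the cost of a full change-from-baseline contrast.** Three baseline years add 2/452 = 0.0044 to the variance at d = 0.
- SE: √(0.00498 + 0.00442) = 0.0969, which is 1.37 times larger.
- Power: Φ(0.2231/0.0969 − 1.969) = 63% if the regions are truly identical, 64% at a 5% excess and 65% at 10%.

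The follow-up comparison is therefore the more powerful at a 5% excess (70% against 64%) and the weaker at 10% (46% against 65%).

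**The case against.** **The article never says that baseline data are excluded.** It is a condensed account, and a statistician is to determine the analysis plan, so a fuller plan may use them. This stands as a limit on confidence. However, the article does more than stay silent: it names the contrast and the adjustment variables, and it defines regional characteristics without the baseline outcome.

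**A reader might infer that intervention regions start higher because the objective says so.** The documents do not support that. Group 1 contains its own controls: regions of both kinds are selected within it, Table 1 gives it a control rate, and the primary comparison is made inside it. A group that includes its controls cannot be defined as higher than them. The phrase is more plausibly a loose way to set high-rate areas (30 per 100,000) apart from highly populated ones (20 per 100,000).

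**Regions are selected for similar incidence.** This also stands: large differences are unlikely, and assuming equal rates for power is consistent with that rule rather than an error. But similarity judged on a few regions does not guarantee agreement within 5% to 10%.

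**The calculation is unadjusted.** True. The differences shown must be read as what remains after adjustment for sex, age and regional characteristics; a crude difference of the same size would do less damage.

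**Change from baseline is not free.** It costs power when matching is good. Selecting on past rates and then differencing against a noisy baseline also invites regression to the mean. This argues against requiring it as the primary estimate.

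**Conclusion.** The concern holds in limited form. As written, the primary analysis of a non-randomised comparison omits the baseline rate of its own outcome although that information is in hand. A residual difference of 5% to 10% would be enough to take power from about 88% to 70% or 46%. With no effect, a 10% difference would raise the one-directional false-positive rate from 2.45% to between 31% and 33%.

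These figures rest on an assumed 1:1 split, 3 years, alpha 0.049, Poisson error only and assumed baseline differences. Extra variation between regions would lower the power figures further. They show sensitivity to an imbalance and are not evidence that one exists.

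The Group 1 wording is a separate and smaller matter: the objectives and Table 1 notes conflict with the selection rules and need reconciling. The point should be fixed, with moderate confidence, because an analysis plan that is not shown might already deal with it.

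**What to change.** 1. Add each region's baseline incidence of the primary outcome to the primary adjustment model, for example as the log baseline rate, by sex and age where available, and fix this before the interim analysis. The article lists severity among the ambulance items collected during the study but does not state it for the baseline records. If it is missing there, the closest available baseline rate should be specified.
2. Prespecify the baseline-to-follow-up ratio of rate ratios as a supporting analysis, and state that regression to the mean and differing trends can affect it.
3. Recalculate the power statement for the estimator chosen.
4. Reword the Group 1 definition in the objectives and Table 1 notes so that it agrees with the selection of similar control regions within Group 1.

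**Cost.** No new type of data is needed; the change is to wording and modelling. Some precision is lost. A full change-from-baseline contrast would have about 63% power if regions were identical. A baseline covariate would probably fall between that and 88%, but this was not calculated. Group 1 draws on only four areas, so few region-level covariates can be supported, and the baseline rate may have to take precedence over some regional characteristics.

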## Methods/Design

A community intervention trial will be conducted to evaluate the effectiveness of a novel suicide intervention program. In this study, the incidence of suicidal behavior in an intervention group and a control group will be compared.

### Organization

The Japan Ministry of Health, Labour, and Welfare selected the Japan Foundation for Neuroscience and Mental Health (JFNMH) as the primary institution responsible for the strategic research program for suicide prevention. The JFNMH conducts the program "Japanese Multimodal Intervention Trials for Suicide Prevention, J-MISP" in close collaboration with the National Center of Neurology and Psychiatry. NOCOMIT-J is one of two research projects being conducted by J-MISP. The other is a randomized, controlled, multicenter trial of post-suicide attempt case management for prevention of further attempts in Japan (ACTION-J).

The principal investigator of NOCOMIT-J and the sub-leader will supervise the study group in order to conduct and complete the study effectively.

The study group management office will engage in overall administrative procedures regarding the operation of the study group. It will also set up and operate the study group steering committee and the intervention program committees, hold the research conference, and respond to questions from institutions in the participating regions.

The J-MISP director, the principal investigator of the NOCOMIT-J, and the regional leaders share the information and collaborate to resolve problems and safety issues with the help of the steering committee and the Central and Local Research Ethics Committee.

The study group steering committee will be composed of regional leaders and other key members of the study group. Research meetings will be held upon the principal investigator's request. At the meetings, the intervention program committee will present the agenda, after which important issues, such as revision of the protocol or stopping of the study, will be discussed.

### Participants and Participating Areas

#### Participants

The participants will include Japanese and foreign residents living in the intervention and control regions.

#### Eligibility Criteria

Target areas will be selected and divided into two groups: "Group 1" and "Group 2" as mentioned above. The areas meeting the following criteria will be eligible for the study:

a) Areas with strong support from local government and other organizations to conduct this multimodal suicide prevention program.

b) Areas capable of selecting intervention and control regions.

c) Areas capable of following the data collection procedure.

d) Areas with comparable baseline data on suicide attempts in intervention and control regions.

e) Areas with comparable baseline demographic data in intervention and control regions.

